## Abstract

**Background:**

Major depressive disorder (MDD) is a highly prevalent mental disorder with large disease burden, high levels of relapse or persistence, and overall suboptimal outcomes of protocolized pharmacological and psychotherapeutic treatments. There is an urgent need to improve treatment effectiveness, possibly through systematic treatment personalization. In psychotherapeutic treatments this can be achieved by case conceptualization. To support this process, we developed the Therap-i module, which consists of personalized Experienced Sampling Methodology (ESM) and feedback. The Therap-i module is integrated into outpatient psychotherapeutic treatment as usual (TAU) for depression. The study aim is to investigate the efficacy of the Therap-i module in decreasing symptomatology in unresponsive or relapsing patients diagnosed with MDD. We hypothesize that the Therap-i module will contribute to TAU by i) decreasing depressive symptoms, and ii) improving general functioning, therapeutic working alliance, and illness perception. This paper provides details of the study rationale, aims, procedures, and a discussion on potential pitfalls and promises of the module.

**Methods:**

Patients diagnosed with MDD (*n* = 100) will enrol in a pragmatic two-armed randomized controlled trial. Randomization is stratified according to the patient’s treatment resistance level assessed with the Dutch Method for quantification of Treatment Resistance in Depression (DM-TRD). All fill-out the Inventory of Depressive Symptomatology Self Report (IDS-SR), Outcome Questionnaire (OQ-45), Illness Perception Questionnaire Mental Health (IPQ-MH), and Work Alliance Inventory Self Report (WAI-SR). In the intervention arm, through close collaboration between patient, clinician, and researcher, a personalized ESM diary is developed based on the patient’s case conceptualization. During the ESM monitoring period (8 weeks, 5 assessments/day), patients receive feedback three times, which is discussed among the abovementioned three parties. Both patients and clinicians will evaluate the Therap-i module.

**Results:**

Data collection is ongoing.

**Discussion:**

This is the first study in which personalized ESM and feedback is integrated in outpatient psychotherapeutic TAU for depression. The labour intensive procedure and methodological pitfalls are anticipated challenges and were taken into account when designing the study. When hypotheses are confirmed, the Therap-i module may advance treatment for depression by providing insights into personalized patterns driving or perpetuating depressive complaints.

**Trial registration:**

Trial NL7190 (NTR7381), registered prospectively 03-08-2018.

**Supplementary Information:**

The online version contains supplementary material available at 10.1186/s12888-021-03123-3.

## Background

Major depressive disorder (MDD) is a highly prevalent mental disorder with large disease burden for patients, their relatives, and society [1, 2]. Due to its intermittent course, where remission is often followed by relapse [3] or persistence of depressive complaints, there is a large and growing need to improve treatment outcome. This is particularly the case for those who have been unresponsive, or insufficiently responsive, to stepwise protocolized pharmacological and psychotherapeutic treatments [4]. These patients are considered difficult-to-treat and further personalization of treatment is needed. Clinicians typically personalize psychological treatment through (re-)investment in a patientۥ s case conceptualization [5]. In case conceptualization patients and clinicians develop a holistic working theory about the patient’s psychopathology.

The core feature of case conceptualization is the active participation of both the patient and clinician. In close collaboration, both combine their unique expertise to describe and explain the patient’s psychopathology in a holistic theory, or case concept. In short, case conceptualization involves: i) describing the presenting patient’s psychopathology, ii) providing a working hypothesis about the psychological mechanisms that drive or maintain a patient’s psychopathology, iii) organizing and integrating patient information based on the judgment of the clinician, and iv) informing diagnosis and treatment [5]. However, although well-established, there is no gold standard for the methodology and theoretical basis of case conceptualization [5–7]. This results in a lack of consensus on the essential features of case conceptualization and low inter-rater reliability between case concepts of different clinicians [8, 9]. Contributing factors might be that a case concept is based on retrospective information and depends on the questions asked by a particular clinician. These issues can be addressed by systematic momentary monitoring in a patient’s normal daily-life and subsequently providing feedback on this information during a subsequent regular consult. A scientific method to obtain this goal is the experienced sampling method (ESM).

ESM involves repeated sampling of momentary affect, cognitions, and/or behavior, typically via a patient’s own smartphone [10]. Prolonged ESM monitoring (i.e., weeks, months) results in time-series data, which can reveal the dynamic course of psychopathology in individuals [11, 12]. ESM holds the promise to advance the case conceptualization process for notable reasons: i) ESM provides patients and clinicians access to momentary information, thereby reducing retrospective bias [10, 13, 14]; ii) ESM promotes the patients’ reflections and insights in his/her own psychopathology by intensive self-monitoring [15]; and iii) ESM derived time-series data can be summarized into personalized feedback reports with intuitive visualizations of the course of the data (e.g., [16]). Such feedback may be further improved through more sophisticated analyses on the time-series data. A method that may hold particular promise for case conceptualization are person-specific network models [17, 18]. Proof-of-principle studies showed that results from such network models may be used as a starting point for a dialog between the patient and clinician during regular consults (e.g. [16, 19, 20].

The efficacy of ESM-based feedback as a therapeutic tool in decreasing depressive symptoms in outpatients diagnosed with depression was first shown in a pioneer randomized controlled trial (RCT, *n* = 102 [21];). The treatment as usual (TAU) condition primarily consisted of pharmacotherapy, with less than 10% of the patients receiving additional psychotherapeutic treatment. In the experimental condition of this study, patients received TAU and monitored their momentary positive affect for 6 weeks. Every week a feedback report was generated from the collected time-series data by a clinical researcher, who discussed the feedback with the patient and his/her clinician. In another, more recent pragmatic RCT in patients indicated for treatment for depression (*n* = 161, [22, 23]), efficacy of ESM-based feedback added to pharmacological and/or psychotherapeutic TAU was not established. In this study, patients monitored their momentary positive and negative affect for 4 weeks. ESM monitoring started after the intake procedure while the patient was waiting for psychotherapeutic treatment, continued monitoring during treatment and weekly feedback was emailed to the patient. The fourth feedback report was discussed with the patient and a research assistant. The authors concluded that, while ESM-based feedback in depression treatment was highly appreciated by both patients and clinicians in their study, its promise to augment the efficacy of regular depression treatment was not met. However, they cannot rule out that it advanced other domains (e.g. acquire better self-insight), or provided a more efficient way of delivering care (i.e. more patients may be treated when combining face-to-face sessions with ESM compared to full face-to-face treatment). Besides notable differences between the two ESM studies outlined above [21, 23], they have in common that ESM was neither personalized nor fully integrated into patient’s psychotherapeutic treatment.

Interestingly, recent research findings from patients and clinicians stress the importance of personalizing ESM assessment and feedback [15]. Furthermore, Bos and colleagues recommended that ESM should be implemented by an interdisciplinary team of patients, clinicians, researchers, and information technology specialists. These recommendations are in line with the clinical process of case conceptualization outlined above. The present study follows these recommendations by implementing them in a new ESM-based intervention: the Therap-i module. In Therap-i fixed ESM items will be supplemented with personalized items to cover core elements of the case concept of each individual. Patients and their clinicians will collaborate, together with the researcher, in personalizing ESM and, discussing ESM-derived feedback results in feedback sessions to advancing the case conceptualization process. Therap-i feedback includes graphs on daily fluctuations of scores on the ESM items, their associations, and contextual information (e.g. notes on (un) pleasurable events, company and activities). Researchers will assist patients and their clinicians during the entire procedure. This approach may anchor the case concepts more robustly in the patient’s narrative during psychotherapeutic treatment.

### Study aims

We aim to test the efficacy of the Therap-i module as a supportive tool in psychotherapeutic TAU in MDD patients, who have been insufficiently responsive to protocolized treatments for depression. We hypothesize that the Therap-i module is effective in these patients in i) decreasing depressive symptom severity (primary outcome), ii) increasing general functioning, iii) increasing the therapeutic working alliance, and iv) improving illness perception (more specifically, increased illness insight, increased personal control over the illness, increased control through treatment, and reduces emotional representation of the illness). After treatment, self-management strategies will be examined and the Therap-i module will be evaluated by both patients and clinicians with quantitative and qualitative instruments. This paper provides a detailed overview of the patient inclusion procedure, instruments, and ESM protocol used in the Therap-i study. Furthermore, potential pitfalls and promises of the module are discussed.

## Methods

### Participants

The Therap-i study is a pragmatic RCT to evaluate the efficacy of the Therap-i module as a tool to support psychological TAU in patients diagnosed with MDD. In the RCT a control group, which receives TAU, is compared with an experimental group, which receives ESM-supported TAU (i.e. the Therap-i module). The design of the Therap-i study is shown in Fig. 1. The trial was registered prospectively on August 3th in 2018 in the Dutch Trial Register (NTR7381, www.trailregister.nl). The study was approved by the Medical Ethical Committee of the University Medical Center Groningen (UMCG, METc2018/434). All patients provide written informed consent prior to participation. According to UMCG policies for studies with negligible risk, an UMCG study monitor was appointed and a monitoring plan was written to assure quality of research. All investigators working on the study have received training and are certified in study conduct, informed consent, and risk assessment (BROK® certified).

**Fig. 1 Fig1:**
[figure not shown]
The *Therap-i* study design (upper part l) and the scheduled questionnaire assessments (lower part). Details are given in the method section. Note: TAU, treatment as usual; prep. ESM, preparation experience sampling method

The in- and exclusion criteria are given in Table 1. We aim to recruit 100 outpatients diagnosed with MDD, who have been unresponsive, or insufficiently responsive, to current or past protocolized psychotherapeutic treatments. Patients are recruited from multiple mental health care institutions in the North of the Netherlands. Patients are eligible for participation if they are starting with outpatient psychotherapeutic treatment, or if they are currently in treatment and their clinician decides to re-invest in case conceptualization and to personalize treatment. No limitations are applied regarding TAU, although use of medication and psychological interventions will be systematically monitored. Patients are informed that participation is voluntary and that not participating will not affect their TAU. Patients will be rewarded with €30 for their participation.

**Table 1 Tab1:** Eligibility criteria for enrolment in the *Therap-i* study

Inclusion criteria	Exclusion criteria
- Meets a MDD diagnosis according to the Diagnostic Statistical Manual (DSM-V) within the past six month. - Has received a primary protocolled psychological intervention for depression, consisting of four months of (cognitive) behavioural therapy, interpersonal therapy or brief psychodynamic therapy, and which is evaluated as not effective (enough) to repeat or continue by the clinician responsible for the participant. - Receives, or is scheduled to receive, policlinic psychological treatment, with weekly one-on-one consults with a clinician for at least 8 weeks. - Aged between 18 and 65 years.	- Meets a diagnosis of MDD with psychotic features, bipolar disorder, substance use disorder, schizophrenia spectrum and other psychotic disorder, neurocognitive disorder in the past six months. - Has a history of treatment with electroconvulsive therapy. - Insufficient mastery of the Dutch language. - Inability or unwillingness to use a smartphone.

### Procedure

#### Recruitment

Potential participants receive a brochure and a contact consent form from their treating or directing clinician. After consent for contact, researchers contact the patient to provide further information about the study. Eligibility also includes approval of the treating clinician in case a patient is contacted via a directing clinician. After 1 week to consider participation, the patient is contacted again to inquire about their willingness to participate in the study and if so, to conduct a short screening for study eligibility. Research Electronic Data Capture (REDCap) software [24, 25] is used to register all contacts with (potential) participants and to manage logistics of the research procedure. Details on data management are given below.

#### Screening

Prior to enrolment, patients are screened on psychiatric disorders that are listed in the in- and exclusion criteria with the Mini-Schedules for Clinical Assessment in Neuropsychiatry (mini-SCAN) and assessed on treatment resistance with the Dutch Method for quantification of Treatment Resistance in Depression (DM-TRD). The mini-SCAN is a validated semi-structured interview to assess psychiatric disorders [26]. Parts of the interview that are relevant to the diagnoses mentioned in the in- and exclusion criteria, are used to confirm their respective presence or absence. The DM-TRD is a questionnaire to assess the level of treatment resistance in depression [27], which is used for stratification in the study (further details given below).

#### Randomisation and stratification

Randomization is outsourced to the research support office of the UMCG (Data Management & Research IT) and programmed in ALEA FormsVision (www.aleaclinical.eu). Participants are randomly allocated to the experimental or control group (allocation ratio 1:1). Randomization is stratified according to the level of treatment resistance based on the DM-TRD (cut-off score >11, [27]). A random block size will be used with a minimum of 4 and a maximum of 8, resulting in blocks of 4, 6 or 8. After *n* = 25, it is evaluated whether the chosen cut-off for stratification is effective. An adjustment of the cut-off will be considered if the chosen stratification cut-off fails in filling the cells in the randomization blocks. Failure is defined as one stratum containing ≥75% of the included participants. If this is the case, the stratification cut-off score will be replaced with the average DM-TRD score calculated on the participants included until then. This evaluation process is an iterative process, which will be repeated after every *n* = 25 inclusions. Allocation concealment is guaranteed through the use of ALEA FormsVision, making the randomisation sequence unpredictable for investigators. The ultimate goal of this process is to equally distribute the level of treatment resistance of the included patients across the two study groups.

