#### Efficacy of the Therap-i module

The following analysis strategy will be applied to both primary (IDS-SR) and secondary outcomes (OQ-45, IPQ-MH subscales, and WAI-SR). The data have a two-level hierarchical structure, because multiple assessments are clustered within subjects. Therefore, multilevel regression analyses will be used to estimate fixed effects for time, treatment allocation, and their interaction, as well as random intercepts and a random slope for time. In this way, we can examine the effect of time on outcomes (across multiple outcome measurements), the effect of group (2 levels: experimental or control group), and the interaction between time and group separately. Thresholds for statistical significance will be set at *p* < 0.05.

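### Allocation is stratified on DM-TRD, but the stated efficacy model has no DM-TRD term; adding the score and its interaction with time is a free, modest gain

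*Protocol article*

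**What the plan says.** Under Randomisation and stratification, the protocol article allocates patients 1:1 and explains that "Randomization is stratified according to the level of treatment resistance based on the DM-TRD", with an initial cut-off of more than 11. It gives the purpose: "The ultimate goal of this process is to equally distribute the level of treatment resistance of the included patients across the two study groups". The cut-off is reviewed after every 25 inclusions. If one stratum then holds 75% or more of the participants, a change is considered, and in that case "the stratification cut-off score will be replaced with the average DM-TRD score calculated on the participants included until then".

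Under Efficacy of the Therap-i module, one strategy covers the IDS-SR and all secondary outcomes: "multilevel regression analyses will be used to estimate fixed effects for time, treatment allocation, and their interaction". The random part of the model gives each patient an own intercept and an own slope over time. DM-TRD is not among the terms, and no other section says that it will be adjusted for.

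The sample size section powers the within-between (time-by-group) interaction, with T0 counted as one of four repeated occasions.

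**The concern.** Stratified allocation removes most of the chance difference between arms on the stratification factor. A model that ignores the factor still counts its outcome variation as noise. Where the factor is related to the effect being tested, the reported standard error is then larger than the true sampling error. Confidence intervals are too wide, p-values are too large, and some power is left unused.

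This trial expects 80 completers and has a single stratification factor, chosen in a population defined by insufficient response to earlier treatment. A relation between treatment resistance and speed of improvement is plausible, though the article does not quantify one.

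The adjustable cut-off adds a practical difficulty. If it is replaced, two patients with the same DM-TRD score can carry different stratum labels depending on when they enrolled. The label then no longer measures resistance on one scale.

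**Working it through.** **1. The plan's own figure.** Inputs from Sample size calculation and withdrawal: Cohen's f 0.14–0.15, N = 80, m = 4 occasions, correlation ρ = 0.5, alpha 0.05, two groups.

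- Noncentrality λ = f²·N·m/(1 − ρ), with df1 = (2 − 1)(4 − 1) = 3 and df2 = (80 − 2)(4 − 1) = 234.
- f = 0.14: λ = 0.0196 × 80 × 4 / 0.5 = 12.54, power 85.1%.
- f = 0.15: λ = 0.0225 × 80 × 4 / 0.5 = 14.40, power 90.0%.
- Dropout: 80/(1 − 0.20) = 100.

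The stated 85–90% and n = 100 reproduce. Neither relies on covariate adjustment.

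**2. DM-TRD as a main effect only.** Mixed models with random intercept and slope were fitted to 40 simulated balanced, complete datasets, with and without a DM-TRD main effect. The time-by-group estimates agreed to about 1e-13 and the ratio of standard errors was 1.000. Some fits gave convergence warnings, but the estimates agreed. The reason is structural: a fixed patient characteristic that shifts the overall level is already absorbed by the random intercept. With dropout the equality is approximate.

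**3. DM-TRD related to the rate of change.** Let R² be the share of variance in individual slopes explained by the DM-TRD stratum. The documents do not give it; 0 to 0.20 is assumed. Take the slope comparison as a z-test, with the standard error reported by the unadjusted model set to 1. Balance on the stratum makes the true standard error q = √(1 − R²). Let d be the effect that gives the target power at R² = 0: d = 1.960 + 1.036 = 2.996 for 85%, and 1.960 + 1.282 = 3.242 for 90%.

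- Type I error, term omitted: 2[1 − Φ(1.960/q)]
- Power, term omitted: Φ((d − 1.960)/q)
- Power, DM-TRD × time included: Φ(d/q − 1.960)

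| R² | q | Type I error, omitted | Power at 85% point, omitted / included | Power at 90% point, omitted / included |
|---|---|---|---|---|
| 0 | 1.000 | 5.0% | 85.0 / 85.0 | 90.0 / 90.0 |
| 0.05 | 0.975 | 4.4% | 85.6 / 86.7 | 90.6 / 91.4 |
| 0.10 | 0.949 | 3.9% | 86.3 / 88.5 | 91.2 / 92.7 |
| 0.20 | 0.894 | 2.8% | 87.7 / 91.8 | 92.4 / 95.2 |

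**4. Simulation of the same comparison.** N = 80, two strata of equal expected size, permuted blocks of 4, 6 or 8 within stratum, 8,000 replicates per setting.

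| R² | Type I error, omitted | Power at 85% point, omitted / included | Power at 90% point, omitted / included |
|---|---|---|---|
| 0 | 5.1–5.3% | 84.0 / 84.0 | 89.8 / 89.8 |
| 0.05 | 4.4–4.9% | 85.8 / 86.9 | 89.4 / 90.3 |
| 0.10 | 3.9–4.2% | 85.4 / 88.0 | 91.0 / 92.7 |
| 0.20 | 2.9–3.1% | 86.8 / 91.1 | 91.2 / 94.4 |

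With the term included, simulated type I error stays at 4.9–5.5% (simulation error about 0.25 points). The power forgone is 0.9–1.1 points at R² = 0.05, 1.7–2.6 at 0.10 and 3.2–4.3 at 0.20, in line with the formulas.

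Steps 3 and 4 test a single slope contrast set to 85% or 90% power. They do not repeat the 3-df F test of step 1. They also use the stratum rather than the continuous score.

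**The case against.** The strongest objection is one of scope. The article outlines the model in one paragraph, covariate lists are commonly left to an analysis plan, and nothing in the paragraph rules out further covariates. This carries weight against calling the omission an error. But the paragraph does name its fixed effects, and a reader who applied it as printed would run an unadjusted analysis of a stratified trial. If an analysis plan adds the term, the article's model description is what needs aligning.

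Four stronger readings are tempting, and the documents do not support them:

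- **That stratification is paid for and not used.** The stated goal is balance between the arms, and allocation itself serves that goal.
- **That all outcome variance due to DM-TRD sits in the error term, so residual variance would fall by the squared correlation with the final score.** That reasoning fits an ANCOVA of a single post-treatment score. The article specifies repeated measures with random intercepts and tests time by group, so variance in level does not enter the test.
- **That the trial falls below its stated power.** The 85–90% takes no credit for adjustment and reproduces without it.
- **That the changeable cut-off makes adjustment unworkable, or leaves imbalance that only a covariate can correct.** A change is conditional on the 75% rule. The stratum used at randomisation could still serve as a factor, and chance imbalance is covered by randomisation-based inference.

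It also stands that the documents offer no evidence that DM-TRD predicts rate of change. If it does not, nothing is lost by leaving it out.

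**Conclusion.** The mismatch between design and stated model is real, and its effect is small and in one direction. Omitting DM-TRD neither biases the treatment effect nor makes false positives more likely, and the sample size stands. If DM-TRD predicts rate of change, the time-by-group test becomes conservative, with a type I error of roughly 3–5% instead of 5%. It then forgoes about 1, 2–3 or 3–4 points of power at a slope R² of 0.05, 0.10 or 0.20.

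These sizes rest on the assumed R², on 80 patients with complete data and on two strata of about equal size. This is an efficiency and alignment point, worth making because the improvement is free.

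**What to change.** In Efficacy of the Therap-i module, add the continuous DM-TRD score and its interaction with time as pre-specified fixed effects in the models for the IDS-SR and every secondary outcome. Include the interaction whether time is linear or categorical, since that term is what can sharpen the time-by-group test.

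Use the score rather than the stratum label, so that the covariate means the same for every patient even if the cut-off is replaced. Settle this before any unblinded analysis, and align any separate analysis plan with it.

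The cost is one or a few degrees of freedom, depending on how time is coded. DM-TRD is already assessed before enrolment, so no new data are needed, and the sample size does not change.
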